## Abstract

Tuberculosis (TB) caused 1.5 million deaths in 2020, making it the leading infectious killer after COVID-19. Bacille Calmette-Guerin (BCG) is the only licensed vaccine against TB but has sub-optimal efficacy against pulmonary TB and reduced effectiveness in regions close to the equator with high burden. Efforts to find novel vaccines are hampered due to the need for large-scale, prolonged, and costly clinical trials. Controlled human infection models (CHIMs) for TB may be used to accelerate vaccine development by ensuring only the most promising vaccine candidates are selected for phase 3 trials, but it is not currently possible to give participants
*Mycobacterium tuberculosis* as a challenge agent.

This study aims to replicate and refine an established BCG CHIM at the Liverpool School of Tropical Medicine. Participants will receive an intradermal injection with licensed BCG vaccine (Statens Serum Institut strain). In phase A, participants will undergo punch biopsy two weeks after administration, paired with minimally invasive methods of skin sampling (skin swab, microbiopsy, skin scrape). BCG detection by classical culture and molecular methods will be compared between these techniques and gold standard punch biopsy. Techniques meeting our pre-defined sensitivity and specificity criteria will be applied in Phase B to longitudinally assess intradermal BCG growth two, seven and fourteen days after administration. We will also measure compartmental immune responses in skin, blood and respiratory mucosa in Phase B.

This feasibility study will transfer and refine an existing and safe model of BCG controlled human infection. Longitudinal BCG quantification has the potential to increase model sensitivity to detect vaccine and therapeutic responses. If successful, we aim to transfer the model to Malawi in future studies, a setting with endemic TB disease, to accelerate development of vaccines and therapeutics relevant for underserved populations who stand to benefit the most.

**Registration:** ISRCTN:
ISRCTN94098600 and ClinicalTrials.gov:
NCT05820594

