**Nasopharyngeal and throat swab ± saliva** Nasopharyngeal and throat combined swab will be obtained during screening visits and prior to BCG challenge (using a rapid antigen test). The aim is to determine viral infection and recognise potential asymptomatic COVID-19 cases and protect the study participants and staff. IThe PCR tests will be performed in batch at study completion and will not be used to inform study procedures.

3.   
**Blood sampling** will be performed by trained, experienced staff. Blood volumes taken at each visit are based on the safety blood screening requirements and planned exploratory immunological investigations. The total clinical blood samples taken at each visit will be 50mls, which is a maximum of 350mls over the study.

4.   
**Punch biopsy** on the intradermal injection site will be performed according to routine dermatological procedures
^
20
^. Local anaesthetic injection will be required and one to two sutures to close the biopsy site. This procedure is planned to take place in both phase A (n=10 participants) and phase B (n=20 participants) and will be used as the gold standard comparator for minimally invasive skin sampling techniques. Written consent will be taken on the same day as the procedure. The procedure will be carried out by an appropriately trained doctor or nurse experienced in this procedure.

5.   
**Minimally invasive skin biopsy** on the intradermal injection site will be performed according to published procedures
^
17
^. This procedure is well tolerated by participants, does not require local anaesthetic; and does not leave a scar. Longitudinal sampling will be performed in Phase B with two microbiopsies taken at each time point (D0, D2, D7 and D14) circumferentially around the edge of the intradermal injection site taken at intervals described in
Table 1, avoiding previous biopsy sites.

6.   
**Skin scrape** on the intradermal injection site will be performed using a rhinoprobe (see nasal sampling) curette. Our group has established standardised operating procedures using this curette for nasal sampling
^
18
^. The procedure is minimally invasive and well tolerated by participants for nasal sampling. This will not be conducted in phase B.

7.   

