•   Similar pattern of response to that seen to BCG intradermal injection, or

3 = Definite

•   Reasonable temporal relationship to BCG intradermal injection and

•   Event not readily produced by alternative aetiology (clinical, environment, or other interventions), and

•   Known pattern of response to BCG intradermal injection.

The chief investigator (CI), with the consultation of the trial steering committee (TSC), if required, will determine causality of AEs. The greatest degree of causal relationship (definite > probable > possible > unlikely related > not related) determined by either the PI or TSC after their discussions will determine the ultimate classification of the AE. Definite (4), probable (3) and possible (2) are considered to be related. No relationship (0) and unlikely (1) are unrelated.

**Table 5. T5:** Expected adverse events.

Expected adverse events
Pain/tenderness at the injection or biopsy site
Redness at the injection or biopsy site
Swelling at the injection or biopsy site
Warmth at the injection or biopsy site
Scaling/pustules at the injection or biopsy site
Transient ipsilateral axillary lymphadenopathy <1cm diameter
Scar at challenge (and biopsy site)
Headache
Fever (>38.3°C)

**
Procedure for recording adverse events
**

Participants will be asked to complete diary cards for 14 days after BCG challenge. They will be provided with a thermometer and tape measure to enable daily recording of temperature and local reactions at the injection site.

The diary cards will be reviewed at follow up visits and adverse events recorded in the CRF. Outside the diary card periods, expected local and systemic AEs (listed in
Table 5) will be specifically asked about and graded by severity (as detailed in
Table 6). Participants will be given the opportunity to report any other new symptoms since the last visit with start and stop dates and any treatments undergone.

All AEs (whether reported by the volunteer or solicited by the Investigator) will be clinically assessed at each visit and recorded in the CRF.

The following information will be recorded: description, date of onset and end date, severity and any treatment or intervention undertaken. The severity of events will be assessed on the following scale: 1 = mild, 2 = moderate, 3 = severe.

An assessment of relatedness to the BCG challenge will then be made by the Investigator.

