AEs considered related to the BCG challenge as judged by a medically qualified investigator or the Sponsor will be followed either until resolution, or the event is considered stable.

**Table 6. T6:** Grading of adverse events.

Adverse Event	Grade	Measurement
Pain/tenderness at the injection or biopsy site	0 1 2 3	No pain at all Painful on touch, easily tolerated Painful when limb is moved, interferes with daily activity Severe pain at rest, interferes with daily activity
Redness at the injection or biopsy site	0 1 2 3	0mm 1–50mm 51–100mm >100mm
Swelling at the injection or biopsy site	0 1 2 3	0mm 1–20mm 21–50mm >50mm
Fever (oral)	0 1 2 3	≤37.5°C 37.6 – 38.0°C 38.1 – 38.9°C ≥39.0°C
Other AEs	0 1 2 3	Absence of symptom Awareness of symptom but tolerated; transient or mild discomfort; little or no medical intervention required Mild to moderate discomfort leading to interference with usual activity, some minimal medical intervention/therapy may be required. Significant interference with daily activity; some assistance usually required; medical intervention/therapy required; hospitalisation possible

**
Reporting procedures for Serious Adverse Events (SAEs) and Suspected Unexpected Serious Adverse Reactions (SUSARs)
**

Any serious adverse event considered by the CI to be related to the challenge agent and unexpected will be reported to the REC. As the challenge agents are vaccines with Marketing Authorisation, the mechanism for reporting any SAEs to the MHRA is via yellow card.

**
Follow up and outcome of adverse events
**

Those adverse events which are unexpected and likely to be related to the BCG, whether serious or not, which persist at the end of the study will be followed up by the Investigator until their resolution. Additional follow-up visits may be arranged to enable this. As appropriate, participants with ongoing AEs may be advised to consult their General Practitioner (National Health Service) or the study team will arrange specialist review within the NHS. The outcome of all related non-serious AEs and any SAEs will be assessed as:

Recovered/resolvedRecovered with sequelae/resolved with sequelaeUnknownOngoing at end of studyFatal

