### Risk assessment

A risk assessment and monitoring plan will be prepared before the study opens and will be reviewed as necessary over the course of the study to reflect significant changes to the protocol or outcomes of monitoring activities. Specific risks are outline below.

**
Phlebotomy
**

The total amount of blood collected over the study period will be a maximum of 350mL. This amount should not compromise otherwise healthy participants. Risks occasionally associated with venepuncture include pain and bruising at the site of venepuncture, light-headedness, and syncope (rarely).

**
Nasal, nasopharyngeal and throat samples
**

This may cause some discomfort, eye watering or a small spot of blood. Participants may swallow the saline during nasal wash which may taste salty.

**
Challenge with BCG SSI
**

Full details are given in the summary of product characteristics (SmPC). In brief:

**
*Local reaction from intradermal BCG injection*
**

•   An inflammatory reaction as manifested by redness and swelling is expected to occur at the site of injection, followed by a local lesion that may ulcerate to be moist for up to three weeks. This heals over some weeks to months to leave a small flat scar. It is also possible to develop some swelling (<1cm diameter) of axillary lymph nodes.

•   Uncommonly (less than 1 in 100 people) swelling of axillary lymph nodes to more than 1cm across, or an ulcer that discharges fluid at the injection site may occur.

•   Rare side effects (less than 1 in 1000 people) include inflammation of lymph nodes leading to abscesses and discharge of fluid from the swellings.

**
*Systemic reactions*
**

•   Systemic reactions to BCG are rare (less than 1 in 1000 people) and include low-grade fever and headache, and allergic reactions. Disseminated complications of BCG, such as bone infections, have also been reported, but are extremely rare and have usually been reported in immunocompromised, not immunocompetent, individuals.

**
*Allergic reactions*
**

•   Allergic reactions from mild to severe may occur in response to any constituent of a medicinal product. Anaphylaxis is extremely rare but can occur.

**
Skin biopsy
**

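### Local reactions are graded on one joint injection-or-biopsy-site item and judged only against BCG, so challenge and sampling effects mix after the Phase A punch and throughout Phase B

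*Protocol article*

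**What the plan says.** In the Safety reporting section, Table 6 gives three local items (pain or tenderness, "Redness at the injection or biopsy site" and "Swelling at the injection or biopsy site"), each with a single 0-3 scale. Table 5 words its expected local events in the same joint way and adds scaling or pustules and "Warmth at the injection or biopsy site". Neither table has an inflammatory item for the biopsy wound alone.

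For each event the plan keeps "description, date of onset and end date, severity and any treatment or intervention undertaken". The investigator then judges relatedness to the BCG challenge. No judgement of relatedness to a biopsy is described.

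Under Clinical samples, the punch biopsy is taken "on the intradermal injection site will be performed according to routine dermatological procedures". The Abstract and Table 2 place it two weeks after challenge. Microbiopsies in Phase B are taken in pairs on D0, D2, D7 and D14, "circumferentially around the edge of the intradermal injection site".

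The Risk assessment expects redness and swelling at the injection site, "followed by a local lesion that may ulcerate to be moist for up to three weeks", with healing over weeks to months.

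**The concern.** The plan asks two safety questions. One is how the skin reacts to BCG at three times the routine dose, a dose the Study design section supports partly by the absence of extra adverse events. The other is how well participants tolerate the sampling. Procedure tolerability is part of the secondary safety objective in Table 1, and the second study hypothesis expects minimally invasive sampling to be more acceptable than the punch.

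Both the challenge and the sampling can produce pain, redness and swelling at the same spot. If these are graded on a joint item and attributed only to BCG or not, a grade after sampling could be read as reactogenicity of the challenge when part of it is wound, or the wound could be absorbed into an expected BCG reaction.

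**Working it through.** No sample size, power or alpha figure is involved. The check sets the schedule against the recording rules.

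**1. When is the site free of biopsy wounds?** (Table 2, Table 7, Clinical samples)

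| | Phase A (n = 10) | Phase B (n = 20) |
|---|---|---|
| Skin sampling before the day-14 visit | Swabs only | Microbiopsies on D0, D2 and D7 |
| Microbiopsies taken before day-14 sampling | 0 | 3 time points × 2 = 6 per participant |
| Post-challenge visits where the site can be inspected with no earlier biopsy | D2, D7, and D14 before sampling (3 of 5) | None of 5 |
| Post-challenge visits after at least one biopsy | D21, D28 (2 of 5) | D2, D7, D14, D21, D28 (5 of 5) |

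So 10 of 30 participants have a biopsy-free period and 20 of 30 have none. This counts a microbiopsy as a wound and a swab as not one.

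**2. How long is the Phase A biopsy-free period?** It is nominally 14 days. With a window of ±2 days around day 14 alone, the punch falls on days 12 to 16. The Table 2 legend says timings run from the actual date of the previous visit. If the windows therefore accumulate (1 + 2 + 2 = 5 days), the punch falls between day 14 − 5 = 9 and day 14 + 5 = 19. On either reading the period is at least about 9 days.

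**3. Does the BCG reaction overlap the punch?** Yes. A lesion that may stay moist for up to three weeks (21 days) and heals over weeks to months is expected to be present on day 14 and afterwards.

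**4. Do the recorded fields separate the two sources?**
- *Dates.* The fields listed are one onset, one end and one severity, with no date for a change of grade. Redness that starts on day 5 at grade 1 and reaches grade 2 after the punch would have a pre-biopsy onset and, if the worst grade is kept, a post-biopsy severity.
- *Diary.* Participants measure local reactions at the injection site daily for 14 days. In Phase A this captures the day-5 grade in the example. It ends nominally on the day of the punch, and afterwards the joint Table 5 items are asked about at visits.
- *Causality.* Other interventions count as an alternative cause. Read literally, levels 0 and 1 require that the event does not follow the recognised BCG pattern, and levels 2 and 3 require that it is not readily explained by another intervention. Redness after a punch through a BCG lesion follows the BCG pattern and is readily explained by the punch, so it fits no level cleanly.

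**5. Result.** Phase A before the punch can be separated with data already planned. Phase A after the punch and all of Phase B follow-up cannot be cleanly attributed from the fields described.

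Punch biopsy in Phase B is described inconsistently: Clinical samples and Table 7 include it, while the Study design text speaks of substituting for it. The Phase B result here does not depend on that, because the microbiopsies start on D0.

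**The case against.** The strongest reply is that Table 6 is a grading scale, not a CRF. The joint wording can mean one scale applied to whichever site is affected, each event has a free description, and a journal article may leave CRF layout to the full protocol. That stands. A reader might infer that the BCG reaction and the wound are entered as one record with one grade, but the article does not say so.

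Second, other local data exist: the daily tape-measure diary, clinical assessment at each visit, and inspection with a photograph at every visit from D0. This also stands. It defeats the stronger inference that challenge reactogenicity can never be separated, or that no later analysis could recover it, because Phase A before the punch is recoverable.

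Third, no progression parameter uses a Table 6 grade. They ask whether participants tolerate procedures and whether a challenge-related SAE or SUSAR occurs. That is correct, so a claim that joint grading would distort the move to Phase B is not supported.

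Fourth, the overlap arises because the biopsy is taken on the lesion, so relabelling alone cannot resolve it, and treating everything after the punch as procedure harm would credit continuing BCG reaction to the biopsy. That stands and limits what the fix may claim.

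Fifth, microbiopsies are described as well tolerated and leaving no scar, so their contribution in Phase B may be small. This is possible, but it is one of the things the study should show.

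What the reply does not answer is that no judgement of relatedness to the procedure is described, and no split of local reactions by biopsy exposure is stated.

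**Conclusion.** The point holds in limited form. Local reactions after the punch in Phase A, and throughout Phase B follow-up, mix challenge and sampling effects; they are graded on joint items and attributed only in relation to BCG. Phase A before the punch (10 participants, nominally 14 days) is separable, but the plan does not say it will be reported separately.

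The affected data are 2 of 5 post-challenge visits in Phase A and 5 of 5 in Phase B. By how much biopsies raise a local grade is not given, so no size of bias can be stated. The primary recovery endpoint is untouched. This should be corrected because it limits the reading of a stated safety objective and costs little.

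The conclusion assumes that the fields named in the article are those used, and that a microbiopsy at the lesion edge can add to local pain, redness or swelling. If the full protocol or CRF already records site and procedure relatedness, only the reporting split remains to be stated.

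**What to change.** - At each visit, grade the site before any sampling. Table 2 already schedules inspection and a photograph from D0, so no new participant procedure is needed.
- Record injection-site and biopsy-site reactions (punch and microbiopsy) as separate items, each with its timing relative to the biopsy.
- Add a judgement of relatedness to the procedure beside relatedness to BCG. Reconcile the causality scale at the same time: it is defined from 0 to 3 and then applied with definite as 4, probable as 3 and possible as 2.
- Report the Phase A peak local grade up to the day-14 pre-sampling inspection as the challenge reactogenicity result. Show post-punch Phase A and all of Phase B separately, labelled as combined challenge-plus-sampling periods.
- Do not close the injection-site item at the punch, and do not attribute later reactions wholly to the procedure.

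The cost is a few CRF rows and one more safety table; the Study status section says recruitment had not begun at submission. The main downside is precision, because the clean estimate rests on 10 people. As an illustration, assuming an exact two-sided 95% interval, observing no event of a given grade in 10 leaves an upper limit of 1 − 0.025^(1/10) = 0.31. Separate items will also not fully disentangle reactions at one location after the punch, which is why those periods should be labelled as combined.

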### Study design

Prospective longitudinal controlled human infection study after intradermal injection with BCG SSI in two phases: Phase A is designed to confirm microbiological recovery and determine agreement between the current gold standard of skin punch biopsy 14 days after injection with minimally invasive biopsy techniques. Phase B is designed to refine and optimise immunological assays to measure local (using optimal minimally invasive techniques), systemic (blood) and respiratory mucosal responses to intradermal BCG injection.

**
Phase A
**

Ten participants will receive a single intradermal injection to the upper arm of BCG SSI 6–24 × 10
^5^ colony forming units in line with an optimised and established existing protocol
^
15
^. The BCG SSI strain has been chosen as the UK licensed vaccine for TB. The dose (3x higher than that used in routine vaccination) has been chosen based on study findings by Minhinnick
*et al.*
^
15
^, who demonstrated good mycobacterial recovery at this concentration with no increase in participant adverse events between the doses. Participants will be followed up longitudinally with active assessment for tolerability; adverse events; and serious adverse events. We will determine BCG SSI recovery from the intradermal injection site 14 days later by classical microbiology and molecular diagnostic techniques using gold standard punch biopsy
^
15
^ as our primary outcome measure. In parallel, and after local anaesthetic injection, we will obtain paired minimally invasive samples (skin swab, skin scrape
^
18
^ and microbiopsy
^
17
^ from the same skin site at 14 days and determine agreement of BCG SSI recovery by classical microbiology and molecular diagnostic techniques with punch biopsy

Parameters for progression from Phase A to Phase B are:

1.Participants able to tolerate study procedures2.No experimental challenge related SAE or SUSAR detected3.Confirmation of BCG recovery by classical microbiology or molecular techniques from punch biopsy at day 14 in all 10 participants who received intradermal BCG challenge4.Confirmation of BCG recovery by classical microbiology or molecular techniques from any of the minimally invasive skin sample technique (swab, scrape and microbiopsy) at day 14 in ≥9 participants who received intradermal BCG challenge.

**
Phase B
**

Twenty participants will receive a single intradermal injection to the upper arm of BCG SSI 6–24 × 10

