### Safety reporting

**
Definition of serious adverse events
**

Our safety reporting terms and definitions are described in
Table 4

**Table 4. T4:** Safety definitions. NB: to avoid confusion or misunderstanding of the difference between the terms “serious” and “severe”, the following note of clarification is provided: “Severe” is often used to describe intensity of a specific event, which may be of relatively minor medical significance. “Seriousness” is the regulatory definition supplied above.

Term	Definition
**Adverse Event (AE)**	Any untoward medical occurrence in a participant to whom a medicinal product or challenge agent has been administered, including occurrences, which are not necessarily caused by or related to that product.
**Adverse Reaction (AR)**	An untoward and unintended response in a participant to an investigational medicinal product or challenge agent which is related to any dose administered to that participant. The phrase "response to an investigational medicinal product or challenge agent" means that a causal relationship between a trial medication/challenge agent and an AE is at least a reasonable possibility, i.e. the relationship cannot be ruled out. All cases judged by either the reporting medically qualified professional or the Sponsor as having a reasonable suspected causal relationship to the trial medication/challenge agent qualify as adverse reactions. It is important to note that this is entirely separate to the known side effects for the challenge agent. It is specifically a temporal relationship between administration of challenge agent, the half-life, and the time of the event or any valid alternative aetiology that would explain the event.
**Adverse Event of** **Special Interest ** **(AESI)**	An adverse event of special interest (serious or non-serious) is one of scientific and medical concern specific to the challenge agent, for which ongoing monitoring and rapid communication by the investigator to the Sponsor can be appropriate. Such an event might warrant further investigation in order to characterise and understand it. Depending on the nature of the event, rapid communication by the trial Sponsor to other parties (e.g., regulators, DSMC) might also be warranted.

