**Serious Adverse** **Event (SAE)**	A serious adverse event is any untoward medical occurrence that: • Results in death • Is life-threatening • Requires inpatient hospitalisation or prolongation of existing hospitalisation • Results in persistent or significant disability/incapacity • Consists of a congenital anomaly or birth defect Other ‘important medical events’ may also be considered serious if they jeopardise the participant or require an intervention to prevent one of the above consequences. NOTE: The term "life-threatening" in the definition of "serious" refers to an event in which the participant was at risk of death at the time of the event; it does not refer to an event which hypothetically might have caused death if it were more severe.
**Serious Adverse** **Reaction (SAR)**	An adverse event that is both serious and, in the opinion of the reporting Investigator, believed with reasonable probability to be due to one of the trial treatments/challenge agents, based on the information provided.
**Suspected** **Unexpected** **Serious Adverse** **Reactions (SUSAR)**	A serious adverse reaction, the nature and severity of which is not consistent with the information about the challenge agent.

**
Adverse events
**

Table 5 details the expected adverse events of BCG injection and challenge site biopsy

**
Adverse event severity assessment
**

Unexpected adverse events will be recorded and these AEs will be graded by severity as follows (where 0 = absent, 1 = mild, 2 = moderate, 3 = severe).
Table 6 details this process:

**
Causality assessment
**

The relationship of each adverse event to inoculation must be determined by a medically qualified individual within the study team according to the following definitions:

0 = No relationship:

•   No temporal relationship to BCG intradermal injection

•   Definite alternative aetiology (clinical, environmental or other intervention), and

•   Does not follow pattern of recognised response to BCG intradermal injection;.

1 = Unlikely relationship:

•   Unlikely temporal relationship to BCG intradermal injection or;

•   Alternate aetiology likely (clinical, environmental or other intervention), and

•   Does not follow pattern of recognised response to BCG intradermal injection

2= Likely relationship:

•   Reasonable temporal relationship to BCG intradermal injection, and

•   Event not readily explained by alternative aetiology (clinical, environmental or other interventions), and

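### Safety reporting judges whether a serious event is related by conflicting thresholds, deciders and scales, so SAR/SUSAR status and REC reporting can disagree with the final causality classification

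*Protocol article*

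**What the plan says.** The relevant rules are in Safety reporting, with one dependent rule in Study design.

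- **Adverse reaction (Table 4).** The bar is that a causal relationship "is at least a reasonable possibility, i.e. the relationship cannot be ruled out". Either of two parties can meet it: "All cases judged by either the reporting medically qualified professional or the Sponsor as having a reasonable suspected causal relationship".
- **Serious adverse reaction, SAR (Table 4).** The event must be serious and, "in the opinion of the reporting Investigator, believed with reasonable probability to be due to one of the trial treatments/challenge agents".
- **SUSAR (Table 4).** "A serious adverse reaction, the nature and severity of which is not consistent with the information about the challenge agent". A SUSAR must therefore first be an SAR.
- **Causality assessment.** The chief investigator (CI) determines causality and consults the trial steering committee (TSC) if needed. The greatest degree "determined by either the PI or TSC after their discussions will determine the ultimate classification of the AE". Codes 2 to 4 (*possible*, *probable*, *definite*) count as related; codes 0 and 1 do not.
- **Reporting procedures for SAEs and SUSARs.** "Any serious adverse event considered by the CI to be related to the challenge agent and unexpected will be reported to the REC".
- **Progression from Phase A to Phase B, criterion 2 (Study design).** "No experimental challenge related SAE or SUSAR detected". It does not say which relatedness rule applies.

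**The concern.** Relatedness of a serious event should have one answer. Here the threshold, the person who decides and the scale all change from one paragraph to the next, and nothing says which prevails. Two features stand out. The causality bar is higher for serious reactions than for reactions in general. And the trigger for telling the ethics committee is not tied to the classification that the protocol itself calls final.

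At stake are the consistency of the SAR and SUSAR counts with the causality column of the safety table, and whether an unexpected serious event classed as related reaches the REC. Criterion 2 also turns on relatedness without saying how it is judged.

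**Working it through.** No arithmetic applies. The check sets the rules side by side and follows one event through them.

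**Thresholds and deciders**

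| Place | Threshold | Who decides |
|---|---|---|
| Table 4, adverse reaction | reasonable possibility | reporting medically qualified professional or Sponsor |
| Table 4, SAR (and so SUSAR) | reasonable probability | reporting Investigator |
| Causality assessment | *possible* or above | highest of PI and TSC |
| REC reporting | related (threshold not restated), and unexpected | CI |
| Progression criterion 2 | challenge related (no rule named) | not named |

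The Monitoring section lists the CI and the PI as separate members of the Study Management Group, so they cannot simply be assumed to be the same assessor.

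**Causality scale**

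| Code | As defined, level by level | As used for the related/unrelated cut |
|---|---|---|
| 0 | no relationship | no relationship: unrelated |
| 1 | unlikely | unlikely: unrelated |
| 2 | likely | possible: related |
| 3 | definite | probable: related |
| 4 | does not exist | definite: related |

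Codes 2 and 3 change meaning, and *possible* and *probable* have no definition. An assessor who thinks an event possible but not likely has no defined level for it. Rounding down to 1 makes it unrelated; rounding up to 2 makes it related.

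**Case 1: all assessors agree.** An unexpected SAE is judged a reasonable possibility but short of a reasonable probability.
- Table 4: it is an adverse reaction.
- Causality assessment: *possible*, so related.
- Table 4: it is not an SAR, and so cannot be a SUSAR.
- REC rule: met if the CI counts *possible* as related.

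The SAR conflict therefore needs no disagreement between assessors.

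**Case 2: assessors differ.** The CI, PI and reporting Investigator rate an unexpected SAE *unlikely*; the TSC rates it *possible*.
- Causality assessment: the greatest degree is *possible*, so the final classification is related.
- Table 4: the reporting Investigator does not hold a reasonable probability, so it is neither an SAR nor a SUSAR.
- REC rule as worded: the CI does not consider it related, so it is not triggered.
- Criterion 2: failed if the final causality classification governs, which is the natural reading but is not stated.

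**What is not in conflict.** A related but expected SAE stays outside the REC rule by design, because that rule also requires unexpectedness. The problem concerns unexpected SAEs only.

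The TSC, whose rating can settle the matter, is not among the bodies described under Study committees, which covers the Study Management Group and the DSMC.

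**The case against.** The strongest reply is that the sections can be read in sequence. Causality assessment gives the task to the CI and produces a final classification after discussion; the REC rule may simply refer to that outcome. On this reading the decider conflict arises only if a CI sets aside the protocol's own final classification. That is a fair reading, but the text does not say it, and it leaves untouched the difference within Table 4 between the adverse reaction and SAR thresholds.

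A second reply is that on the defined 0 to 3 scale *likely* might be taken to meet a reasonable probability. The gap between the Causality assessment cut and the SAR bar would then close, leaving only the difference in decider. This shows that the answer depends on which of two scales is used, which is itself part of the problem.

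A third reply concerns safeguards, and it stands. The DSMC reviews all SAEs whether or not they are judged related and receives a report when one occurs; the yellow-card route is given for any SAE; and the Introduction reports no SAEs in the earlier intradermal BCG challenge studies. Events would not be hidden, and few are expected. These safeguards do not decide whether an event counts as an SAR or SUSAR or goes to the REC.

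Two stronger readings are tempting and not supported. A reader might infer that one discordant rating flips the decision to proceed to Phase B. A related SAE fails criterion 2 whatever its SAR or SUSAR label, REC reporting is not part of the criterion, and the final causality classification is its natural basis. A reader might also infer that no TSC exists. A condensed article that omits a committee from one section does not show that.

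**Conclusion.** The inconsistency is real and lies in what the protocol states. Followed literally, its rules allow an unexpected SAE to be finally classed as related and yet be neither an SAR nor a SUSAR, nor reportable to the REC. The SAR part follows from the two thresholds in Table 4 alone. The REC part assumes that the CI's view is taken as worded and may differ from the final classification.

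The size is modest and cannot be given as a number: the documents offer no rate of SAEs or of disagreement between assessors. What is exposed is the labelling of serious events in the safety report and REC notification of unexpected ones. For progression, the defect is only that criterion 2 does not name its relatedness rule.

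**What to change.** Reconcile the Phase A progression parameters, Table 4, Causality assessment and the SAE/SUSAR reporting paragraph to a single rule:

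1. Use one causality scale, with every level defined, and state the related/unrelated cut in those same levels and codes.
2. Keep one final classification. Causality assessment already describes its outcome as final; state whether the CI, the PI or both supply a rating, and reconcile the committee named there with those under Study committees.
3. In Table 4, define an SAR as an SAE classed as related by that classification, and a SUSAR as such an event that is also unexpected.
4. Tie the REC trigger to the same classification, together with unexpectedness.
5. State that progression criterion 2 uses it.

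The cost is wording, made through the protocol's own amendment route, with no change to sample size, visits or assays. Study status says that recruitment had not begun at submission. The downside is that slightly more SAEs may be classed as related and reported.
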